H2: The T4TM plus MIHP (intervention group) as compared to the MIHP only (control group) will have: a) higher average maternal responsiveness scores, b) greater probability of using a positive feeding style, and c) greater average delay in introducing solid foods in keeping with AAP guidelines.

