## Methods/Design

### Overall study design

This randomized, experimental, short-term, longitudinal controlled trial uses a convenience sample of low-income adolescent first-time mothers of infants from four counties in Michigan. Participants are randomly assigned to the T4TM intervention or a control group with a retention goal of N = 40 participants per group by Time 3 data collection. Data are collected when infants are 4–8 weeks of age (Time 1), 10–12 weeks of age (Time 2), and 6 months of age (Time 3).

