### Procedures

Data are obtained by trained data collectors using both self-report questionnaires and anthropometric assessment. To ensure consistency and accuracy of data collection, a half-day intensive training session was held for data collectors prior to the collection of data, to be followed by a booster session in year 2. Training consisted of a standardized training guide and protocol including review of the instruments and measurement of infant recumbent length and weight. Telephone contact and email communication occurs between the project manager and the data collector and/or supervisor to facilitate open communication and fidelity to the protocol.

Intervals for data collection reflect time points (at infant age of 4–8 weeks, 3 months, and 6 months old) that align with both infant feeding recommended milestones and the intervention duration. For example, the third data collection occurs when the infant is 6 months old, when solids foods introduction is recommended.

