### Measures

#### Maternal outcomes

**Maternal responsiveness** is defined as sensitivity of the behaviors of a mother to her infant’s cues through expert judgment of what her infant needs [91-95]. These behaviors comprise a relationship skill set promoting mothers’ accurate recognition and response to infants’ feeding cues [96,97]. The Maternal Infant Responsiveness Instrument [125] is used to measure maternal responsiveness to infant cues; the scale is valid [126] and reliable (alpha = .83 and .87) [41,127]. We expect the intervention group to have higher scores than the control group.

**Feeding style** expresses the mother’s beliefs about and approach to guiding her infant’s feeding behaviors [97,98]. It also describes how (style) mothers feed their infants (authoritative, authoritarian, permissive, uninvolved) [99-101]. An adapted version of the Infant Feeding Styles Questionnaire (IFSQ) [128,129] is used to measure feeding beliefs and feeding style behaviors [42,43,97-99,129,130]. The IFSQ was pretested and validated with 150 African American first-time mothers with children ≤ 2 years of age [43]. Reliabilities for subscales range from .75 to.95 [128]. We expect the intervention group to score higher in the authoritative range than the control group.

**Feeding practices** are maternal behaviors relating to what is fed, where, how, and how often; they are essential for ensuring healthy eating habits throughout childhood [98,102-104]. The Infant Feeding Index (IFI) [131-134] identifies age-appropriate beverages and foods offered to the infant [135-138] and the appropriateness of feeding environment (i.e., support infant’s self-regulation) per AAP recommendations is a valid measure [131,133,135,136,139]. Of primary concern is the time at which solid foods are first introduced into the infant’s diet. We expect a longer average delay of introduction to solid foods that is closer to the AAP recommendation in the intervention group compared to the control group.

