### Data analysis

Outcomes (infant growth, MR, FS, FP) and maternal and infant factors at baseline (self-efficacy, knowledge, infant age, temperament, type of feeding) will be compared across intervention and control groups using t-test for continuous variables and chi-square test for categorical variables [149,150]. If differences are observed, the relevant variables will be treated as covariates in our post-experiment analyses [149,151,152]. All analyses will use the intention-to-treat [153] principle based on imputed data. The hypothesis regarding differences in outcomes at each follow-up T2 and T3 between intervention and control groups will be tested using the generalized estimating equation (GEE) model [154] for proportional group differences in growth over time. To explore efficacy of the intervention as assessed by MR, FS, FP, evaluated pre-intervention (T1), immediately post intervention (T2), and when the infant is six months old (T3). Both general linear mixed models (GLMM) [155,156], for continuous outcomes and the GEE model for logistic or Poisson regression for binary/ordinal and count outcomes will be considered.

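### H2c averages the age at first solids, but follow-up stops at the recommended age, so infants not yet on solids at Time 3 are right-censored and the named models do not handle them

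*Protocol article*

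**What the plan says.** Under Aims and hypotheses, H2c sets the feeding-practice comparison as "greater average delay in introducing solid foods in keeping with AAP guidelines". Maternal outcomes repeats the target ("We expect a longer average delay of introduction to solid foods that is closer to the AAP recommendation in the intervention group") and ranks it above the other feeding practices: "Of primary concern is the time at which solid foods are first introduced".

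Overall study design places the third and last data collection at 6 months of age. Procedures explains the choice: "the third data collection occurs when the infant is 6 months old, when solids foods introduction is recommended".

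Data analysis says that maternal responsiveness, feeding style and feeding practices are evaluated at T1, T2 and T3. It names "general linear mixed models (GLMM) [155,156], for continuous outcomes", with GEE for the other outcome types, and leaves the choice open ("for continuous outcomes and the GEE model for logistic or Poisson regression for binary/ordinal and count outcomes will be considered"). All analyses follow intention to treat on imputed data. No time-to-event method is named.

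**The concern.** Age at first solids is the time of a single event. The article asks for its average and stops observing at the age up to which the intervention encourages mothers to wait. For an infant not yet on solids at T3, the data say only that the age exceeds the age at that visit. That is censoring, not missingness, and it depends on the outcome: the better the intervention works, the more intervention infants fall into this group.

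An unrestricted mean cannot be recovered from such data without extrapolating beyond 6 months. The two routine ways of forcing it are to analyse only infants with an observed age, or to impute the rest from observed ages. Both remove or pull down the successes. This matters beyond one p-value, because Sample size and power calculations lists the effect size for powering a larger study among the primary foci. An attenuated estimate would carry over into that planning.

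**Working it through.** **Figures in the document.** There is no power, effect size or distribution for H2c, so there is no stated figure to reproduce. The one sample size (40 per group, one-tailed 0.05, power 0.80) concerns infant growth. Only the 40 per group and the one-sided 0.05 are used below.

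**Inputs from the document.** End of observation C = 6 months; 40 per group.

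**Assumed inputs.** Age at first solids normal; control mean 3.5 to 5.0 months; SD 1.0 to 1.5; true delay 0.5 to 1.0 month; everyone seen at T3.

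**Formulas.** For an arm with mean μ and SD σ, let a = (C − μ)/σ, F = Φ(a) and λ = φ(a)/Φ(a).

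- Share without an observed age: 1 − F
- Mean among those observed: μ − σλ
- Mean with ages capped at C: F(μ − σλ) + (1 − F)C

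**Worked example: control mean 4.5, SD 1.5, delay 1.0.**

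- Control: a = 1.00, F = 0.841, λ = 0.288. Observed mean = 4.5 − 1.5 × 0.288 = 4.07. Capped mean = 0.841 × 4.07 + 0.159 × 6 = 4.38.
- Intervention: a = 0.333, F = 0.631, λ = 0.599. Observed mean = 5.5 − 1.5 × 0.599 = 4.60. Capped mean = 0.631 × 4.60 + 0.369 × 6 = 5.12.
- Without an observed age: 16% against 37%.
- Difference with those infants dropped: 0.53 month, 53% of the true 1.0.
- Difference with ages capped: 0.74 month, 74% of the unrestricted difference.

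**Across the assumed range.**

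| Control mean, SD, delay | No age by 6 months (control, intervention) | Kept if dropped | Kept if capped |
|---|---|---|---|
| 3.5, 1.0, 0.5 | 0.6%, 2.3% | 92% | 99% |
| 4.0, 1.5, 0.5 | 9%, 16% | 68% | 88% |
| 4.5, 1.5, 1.0 | 16%, 37% | 53% | 74% |
| 5.0, 1.5, 1.0 | 25%, 50% | 44% | 63% |

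The first and last rows are the extremes of the grid.

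**Imputation.** If ages are imputed from the observed ages in the same arm, the completed mean equals the observed mean in expectation, so the bias is that of dropping. Imputing from both arms pooled shrinks the difference further.

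**Power in the worked example (40 per group, one-sided 0.05).** With full ages 0.91; dropped 0.59; capped 0.88. By simulation, a log-rank test censoring at 6 months has 0.85, and a test on solids by 6 months, yes or no, has 0.71.

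**A different form of effect.** Suppose the intervention leaves most mothers unchanged and moves 20% of the arm to 6.5 months (SD 1.2, control mean 4 or 4.5). If these come from any starters before 6 months, the true gain is 0.53 or 0.45 month and the dropped-case difference is about 0.00. If they come from those who would have started at 4 to 6 months, the true gain is 0.34 or 0.32 and the dropped-case difference is −0.24 or −0.18, the wrong sign.

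**The case against.** The strongest reply is that the article fixes no handling rule. Data analysis assigns age at first solids to no particular model and says only that the model families will be considered. A binary GEE on solids yes or no at each visit would be within its wording, and the coding of infants not yet on solids is normally left to an analysis plan, which is not shown. This stands so far as it goes. A reader might infer that the planned analysis is biased as written; the document does not show that. What it does fix is a mean as the target and 6 months as the end of observation, and no later coding rule makes those two fit without changing the target.

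Other tempting readings also go too far:

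- **That capping at 6 months is itself a flaw.** With everyone seen at T3, the capped mean is the restricted mean time to 6 months. H2c ties the delay to the AAP guidelines, which Procedures places at 6 months, so delay up to that age is a natural target. Capping falls short only against an unrestricted mean.
- **That age at first solids is to be modelled as a repeated measure.** The three evaluations refer to feeding practices as a whole. These are measured by an index that also covers beverages and feeding environment and can sensibly be repeated.
- **That every mother who follows the advice lacks an age.** One who starts at about 6 months, before the visit, has one.
- **That the dates are already in hand.** No section says that a date or age of first solids is recorded.

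**Conclusion.** The point holds in a limited form. H2c asks for an average that follow-up ending at 6 months cannot supply, and the model families named do not handle the censored infants. Under dropping, or imputation from observed ages, the difference is biased towards no effect: 44% to 92% of the true difference is kept across the assumed grid, and the sign can reverse if the intervention works mainly by moving mothers from just before 6 months to after it.

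The mechanism follows from the document; the sizes do not. They rest on assumed normal ages, and the document gives no information on how many infants will still be off solids at T3. If nearly all mothers start early (mean 3.5, SD 1.0, delay 0.5), the loss is about 8% with dropping and 1% with capping. The outcome is one of several maternal outcomes, so this should be corrected but does not undermine the trial's infant outcome.

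**What to change.** Restate H2c as time to first solids, censored at the infant's age at T3.

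- **Estimate:** the difference between arms in restricted mean time to 6 months. When all are seen at T3 this equals the difference in ages capped at 6 months. The anticipated 100 enrolled against 80 retained allows for 100 − 80 = 20 losses, so the survival-curve form is safer, with infants lost earlier censored at last contact.
- **Test:** log-rank or Cox, adjusted for county because randomization is balanced by county.
- **If only solids status at each visit is recorded:** use the interval-censored versions of these methods.
- **Simpler alternative:** compare the proportion without solids at a fixed age before T3.
- **Rule to state:** an infant not yet on solids is treated as censored and is not imputed as missing.

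The cost is a change of wording in the hypothesis and the analysis section, with no added visit. It requires the age at first solids, or solids status at each visit, to be recorded, which should be confirmed. The estimate will describe delay up to 6 months only.

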## Methods/Design

### Overall study design

This randomized, experimental, short-term, longitudinal controlled trial uses a convenience sample of low-income adolescent first-time mothers of infants from four counties in Michigan. Participants are randomly assigned to the T4TM intervention or a control group with a retention goal of N = 40 participants per group by Time 3 data collection. Data are collected when infants are 4–8 weeks of age (Time 1), 10–12 weeks of age (Time 2), and 6 months of age (Time 3).

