**Methods/Design:**

We describe our study protocol for a randomized control trial with an anticipated sample of 100 low-income African- American and Caucasian adolescent, first–time mothers of infants. Participants are recruited through Maternal-Infant Health Programs in four counties in Michigan, USA. Participants are randomly assigned to the intervention or the control group. The intervention provides infant feeding information to mothers via a web-based application, and includes daily behavioral challenges, text message reminders, discussion forums, and website information as a comprehensive social media strategy over 6 weeks. Participants continue to receive usual care during the intervention. Main maternal outcomes include: (a) maternal responsiveness, (b) feeding style, and (c) feeding practices. The primary infant outcome is infant weight. Data collection occurs at baseline, and when the baby is 3 and 6 months old.

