### Aims and hypotheses

The aim of this study is to compare the effect of a social media intervention for low-income adolescent, first-time mothers of infants 2 months of age or younger, versus standard care on infant weight, maternal responsiveness, and feeding style and practices. Adolescent mothers with infants 2 months of age or younger will be assigned randomly to a control/usual care or intervention condition.

The usual Maternal Infant Health Program (MIHP) care only condition consists of voluntary home visits (one week postpartum, six weeks, and six months) and on-going as needed visits (up to nine during the infant’s first year of life) provided by a Registered Nurse (RN), Licensed Social Worker (LSW), Registered Dietician (RD), infant mental health specialist and/or paraprofessional. Maternal Infant Health Program interventions are based on participants’ individualized plans of care following in-home screening assessments. Content includes a flexible plan of care with visits based on identified domains for both the mother (e.g., family planning, transportation, housing, and breastfeeding support), and the infant (e.g., monitoring infant growth). For the T4TM plus usual MIHP care condition, participants get the same usual care treatment as the control group and also receive text messages for six weeks, reminding them to view the T4TM web-application and complete the behavioral challenges. Daily challenges cycle through a pre-determined schedule and focus on: 1) maternal-infant feeding interaction (maternal responsiveness, infant temperament, feeding style); and 2) feeding practices (e.g., delay of early introduction to solids; how much to feed babies) including the feeding environment (e.g., communication with baby, sitting down to eat, turning off the television). Participants also have the option to retroactively complete challenges posted in the last week. We hypothesize:

H1: The T4TM plus MIHP (intervention group) as compared to the MIHP only (control group) will exhibit a greater proportion of infants: a) with a growth in weight that falls below the 85th percentile of the WHO (World Health Organization) growth norms at three and six months, and b) that have a z-score change <0.67 in weight-for-age WHO norms over time periods one to three months, and three to six months [27,88].

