### T4TM intervention

T4TM provides a new daily challenge over six weeks, a time frame selected to provide participants with enough opportunities to form the habit of visiting the T4TM web-application daily [122,123]. Participants log onto T4TM through their cell phones (or a computer), a technological requirement for the study that does not pose an undue burden on participants, especially as low-income households use social networks more frequently than adolescents in higher-income households [71,72]. Participants are encouraged to engage with T4TM as frequently as they like. Frequency of use and number of challenge completion will be logged by the application. Throughout the six-week intervention, participants will receive a daily text message, containing the challenge name and the URL to open the web-application directly through their smartphones. When the participants visit the T4TM page they will see: 1) the name of the challenge, 2) why the challenge is important, 3) tips to complete the challenge, 4) how many people have completed the daily challenge, and 5) a space to leave comments. In addition to the rotating challenges, adolescent mothers can browse T4TM for information about infant feeding, links to related topics, a discussion forum, and a place where they can receive expert advice from a RD or RN. When participants complete a daily challenge, they may click on the “I Did This” button to publicly acknowledge their accomplishment, which serves as a motivational feedback function as they observe other mothers’ completion of the challenges, thereby establishing healthy feeding practices as normative for the young mothers [124]. Participants continue to receive usual MIHP care during the intervention.

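### A six-week intervention started at a 4–8 week baseline ends at 10–14 weeks, so T2 at 10–12 weeks cannot be post-intervention for dyads whose baseline falls after 6 weeks

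*Protocol article*

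**What the plan says.** All references are to the protocol article.

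- **Visit ages.** Overall study design gives "4–8 weeks of age (Time 1), 10–12 weeks of age (Time 2"), with Time 3 at six months.
- **T2 elsewhere.** Procedures places the visits "at infant age of 4–8 weeks, 3 months, and 6 months old". The Abstract says "Data collection occurs at baseline, and when the baby is 3 and 6 months old".
- **Duration.** The T4TM intervention section states "T4TM provides a new daily challenge over six weeks".
- **Start.** Written consent is taken at the initial data collection home visit (Participants and recruitment). The data collectors learn the assigned group only on arriving for that visit (Randomization).
- **Label.** Data analysis treats T1 as pre-intervention and T2 as "immediately post intervention (T2"). The Infant outcome section also labels T2 as post-intervention. Procedures says that the intervals fit the intervention's duration.
- **Growth hypothesis.** H1b applies a 0.67 z-score cut-off "over time periods one to three months, and three to six months".

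**The concern.** The two age windows, the six-week duration and the post-intervention label cannot all hold for every dyad. A late baseline leaves too little time before T2 for the programme to be delivered.

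Three uses of T2 depend on the label:

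- T2 is one of only two follow-ups at which the arms are compared.
- A stated focus of the trial (Sample size and power calculations) is an effect size for planning a larger study. A T2 estimate diluted by partial exposure would tend to understate what the full programme does.
- Acceptability and satisfaction are rated at T2 (Feasibility variables). Some mothers would be rating a programme that they are still receiving.

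A secondary point concerns H1b. The time between T1 and T2 can differ widely between infants, so one fixed change threshold is not the same test for each of them.

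**Working it through.** **Inputs.** Baseline age *a* is 4 to 8 weeks and T2 age *t* is 10 to 12 weeks (Overall study design). The alternative for *t* is 3 months, or 13.04 weeks, taken as 13 (Abstract, Procedures). Duration is 6 weeks (T4TM intervention). The start is assumed to be on the day of T1, which is the most favourable case. The distribution of *a* and the rule that places *t* in its window are not given, so both are assumed and varied below.

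**Step 1: end of intervention.** End = *a* + 6. The earliest is 4 + 6 = 10 weeks and the latest is 8 + 6 = 14 weeks. The lower end agrees with the opening of the T2 window. The upper end is 14 − 12 = 2 weeks past its close.

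**Step 2: who can finish.** Completion by T2 requires *a* ≤ *t* − 6.

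- *t* = 12: *a* ≤ 6, so the upper half of the baseline window (6 to 8 weeks) cannot finish.
- *t* = 13: *a* ≤ 7, so the last quarter (7 to 8 weeks) cannot finish.
- *a* = 8: between 14 − 12 = 2 and 14 − 10 = 4 of the six weeks are still undelivered at a T2 inside 10–12 weeks.

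**Step 3: share incomplete at T2.** With *a* uniform over 4–8, the share incomplete at a fixed *t* is 1 − (*t* − 10)/4. For *t* uniform over 10–12 and independent of *a*, (*t* − 10)/4 averages 1/4, which leaves 75% incomplete.

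| Assumption (start at T1 unless stated) | T2 at 12 weeks | T2 random in 10–12 weeks |
|---|---|---|
| T1 uniform | 50% | 75% |
| T1 in whole weeks, T2 in whole weeks | 40% | 60% |
| T1 skewed early, Beta(1,3) | 13% | 47% |
| T1 skewed late, Beta(3,1) | 87% | 97% |
| T1 uniform, start one week after T1 | 75% | 94% |

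With T1 uniform and T2 at 13 weeks, the share is 1 − 3/4 = 25%.

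**Step 4: amount of exposure.** With both ages uniform and independent, the mean gap is 11 − 6 = 5 weeks. The mean excess of the gap over six weeks is 1/6 week. Mean delivered share = (5 − 1/6)/6 = 0.81.

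**Step 5: interval for H1b.** The shortest gap is 10 − 8 = 2 weeks and the longest is 12 − 4 = 8 weeks, a four-fold range. Under the same uniform assumption, 1/16 of gaps fall below 3 weeks and 1/16 above 7, so 87.5% lie between 3 and 7 weeks.

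**The case against.** A reader might infer that most intervention mothers are measured before the programme ends. The article does not support this. The inference needs a distribution of baseline age and a T2 placed without regard to T1, and neither is stated. Staff who take the post-intervention label seriously would see late-baseline dyads late in the window. Recruiting expectant mothers makes early baselines plausible. If T2 is read as 3 months, the share under uniform T1 is 25%. This objection stands, and the point is confined accordingly to dyads with a baseline after 6 weeks (or about 7).

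A reader might also infer that the comparison of arms is biased. The windows are the same in both arms, so the direct effects are dilution of the T2 contrast and a label that does not fit. On average about 81% of the challenges would have been sent under the uniform assumption. T3, at about 26 weeks, falls well after the latest end of 14 weeks. This also stands and limits the severity.

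On H1b, the four-fold range describes the extremes, and shared windows make the varying interval mainly a source of noise. The z-scores are age-standardised, but that corrects for age at each visit and not for the time allowed for change. The point survives only as a secondary one.

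The gap between 12 weeks and 3 months could be ordinary rounding. It still matters here, because the choice moves the affected share from 50% to 25% under uniform T1.

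None of this removes the conflict. The Abstract's statement that the intervention falls within the first four months of life is compatible with an end at 14 weeks, but it does not make a 10–12 week visit post-intervention.

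**Conclusion.** The point holds in this form: the stated T1 window, T2 window, six-week duration and post-intervention label are mutually inconsistent for any dyad with a baseline after 6 weeks of infant age. With T2 at 3 months, they are inconsistent for any dyad with a baseline after about 7 weeks. This rests only on the article's own figures and on the intervention not starting before T1. A later start makes the mismatch worse.

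The share affected is not known. With start at T1 and T2 at 12 weeks, it is 50% for uniform T1 and runs from 13% to 87% across the skewed distributions tried. The word most would be an assumption and not a finding. The consequence is a T2 estimate and T2 acceptability ratings that mix partial and complete exposure. T3 keeps its meaning as a post-intervention time point. This should be fixed, but it does not undermine the trial as a whole.

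**What to change.** Reconcile the Abstract, H1 in Aims and hypotheses, Overall study design, Procedures, Infant outcome and Data analysis on when T2 takes place. There are two workable routes:

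1. Schedule the T2 assessment no earlier than six weeks after the T1 visit, with a short fixed window after that, identically in both arms. T2 can then be called post-intervention.
2. Keep the age-based window and stop describing T2 as post-intervention.

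In either case, compute z-scores at exact age and adjust for infant age at T1. Data analysis currently lists infant age as a covariate only if the arms differ at baseline. Do not put the T1–T2 interval in the model: it arises after randomisation, and the data collectors know the arm from the baseline visit, so visit timing could differ by arm and the adjustment could introduce bias.

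The cost of route 1 is wording and scheduling. There are no extra visits and the intervention does not change. Some T2 visits move later, to 14 weeks plus the window for a baseline at 8 weeks. T2 age then spreads around three months, which loosens the link to the feeding milestones that Procedures gives as a reason for the timing. H1a's three-month wording should then be restated as age at the T2 visit. Route 2 costs only wording, but it gives up T2 as an end-of-intervention estimate. Either change should be made before T2 data accrue, because a visit made too early cannot be repeated at the right time.
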